##### Exploratory Analyses

We will also conduct exploratory analyses for device-related and nondevice-related HAIs and their main components (to address heterogeneity of risk factors across HAI subtypes). We will quantify the importance of a group of factors in explaining center variability in HAI by fitting models with and without such factors and comparing how well the expected numbers from different models track with the observed numbers. Primary analyses will include all centers, and for the purpose of sensitivity analysis, we will also exclude low-volume centers. We will explore different center volume thresholds, trying to strike a balance between 2 considerations: stable estimate of HAIs rate (quantified by standard error) and number of centers remaining for analysis. We will use simple mean imputation, median imputation, or multiple imputation to account for anticipated missing covariates depending on their pattern and mechanism [50]. If the missing data itself are thought to be related to outcomes, then missing indicators will be used and modeled as independent variables as part of sensitivity analysis.

##### Teamwork and Communication as Quality Measurement

Provider social networks represent a measure of teamwork and communication that are associated with the quality of care [34]. In prior validation work, shared patients between providers, identified using unique provider identifiers found in claims data, have been found to correspond closely to surveyed provider network patterns [33,51]. We will characterize mapped VAD networks using a measure known as assortativity, which can capture the degree to which providers from different specialties and clinical disciplines are interconnected and, thus, better equipped for collaboration and teamwork [52]. We will incorporate this measure as a covariate in our statistical models [34]. Recent network research has drawn attention to several challenges in characterizing assortativity in social networks. First, global (ie, network level) measures of assortativity may mask considerable local (ie, node level) variation in cross-group (eg, specialty) interaction [53]. Second, common network data practices (eg, unipartite projection of a bipartite network) may lead to bias in values of standard assortativity measures [54]. To overcome these challenges, we plan to use state-of-the-art techniques for evaluating assortativity in social networks, including multiscale measures of assortativity (which allow for measuring assortativity at the node level) and comparison of assortativity on our observed networks with null (ie, random network) models.

Claims data do not map perfectly to true care patterns; therefore, our network measures may include false negatives and false positives. To assess for these biases, we will run several sensitivity analyses, motivated by prior work on missing data and thresholding techniques in the study of social networks [55-57]. Using Monte Carlo simulations, we will randomly drop increasingly larger fractions of providers and relationships in our observed networks, recompute our network measures, and then rerun our statistical models to assess bias attributed to false negatives. In additional simulations, we will also gradually add larger fractions of random providers and relationships to our observed networks to assess sensitivity to false positives.

The approaches discussed above consider the time-to-event endpoint (ie, time to first HAI), which counts multiple HAIs from a single patient only once. Alternatively, we will consider the recurrent event endpoint, where multiple HAIs from a single patient are counted multiple times. We will use a counting process, Anderson-Gill model, to rerun the analysis using a recurrent event endpoint to help distinguish the 2 outcome scenarios [58].

### Aim 2: Develop a Comprehensive Understanding of Barriers and Facilitators for Achieving Low Center Health Care–Associated Infection Rates

A mixed methods patient tracer assessment framework will be applied (adapted from the Joint Commission’s tracer methodology) in aim 2 to examine center-level resources and local barriers and facilitators for achieving low HAI rates [59]. We will conduct semistructured interviews, field observations, and document analysis at 5 high-performing (ie, low HAI) and 5 low-performing (ie, high HAI) centers, which we will examine as a mixed methods case series to address this aim.

#### Sampling

A priori, we will use HAI rates derived from aim 1 to intentionally sample 5 high-performing centers with low HAI rates and 5 low-performing centers with high HAI rates for site visits. However, the sampling process will be further refined based on other criteria pending the nature of findings emerging from aim 1 and center-specific practices (eg, measures of provider teamwork).

#### Data Collection

We will conduct 2-day site visits at 5 high-performing and 5 low-performing centers. The mixed methods patient tracer assessment procedure focuses on the patient’s trajectory from the index hospitalization to 90 days. Before site visits, we will conduct advanced analytics to examine performance features, measures, and other quantitative data that will inform qualitative data collection. During the center visits, the site-visiting team will systematically trace the patient’s movement through the health system and investigate HAI risk factors or preventive strategies at each *stop* of the patient’s trajectory (ie, transitions in care or changes in the patient’s physical location). At each site, we will (1) conduct in-depth, semistructured interviews with relevant provider and nonprovider stakeholders and perform field observations of the environment and staff behaviors in the clinical unit and relevant operating room; (2) collect, discuss, and analyze relevant protocol documents; (3) learn local strategies used to enhance HAI prevention; and (4) gather toolkit design elements that would enhance its receptivity and local adoption. These findings will provide a robust understanding of the organizational resources and local facility barriers and facilitators for HAI prevention.

##### Semistructured Interviews

The site-visiting team will follow a patient’s trajectory and conduct semistructured interviews with stakeholders impacting VAD patient care, including administrators (eg, chief medical or nursing officer, quality or safety officer, physician service chief, clinical unit manager, and hospital epidemiologist), physicians (eg, attending surgeon, intensivist, hospitalist, and medical consultants—pulmonologist and cardiologist), advanced practice providers (eg, nurse practitioner and physician assistant), and nurses (eg, ward and intensive care unit). Informed consent will be obtained from informants before starting each interview. Each interview, which will be conducted in private offices or conference rooms, will last for 40 min to 60 min. Stakeholder interviews will focus on answering questions from the advanced analytics, understanding perceptions of the center’s resources and local strategies for HAI prevention, and eliciting key features that would enhance local toolkit adoption. Interviews will continue until reaching informational redundancy or saturation (ie, no new information is being identified) at each center. Following each interview, the study team will provide a gift certificate to each interviewee to acknowledge his or her contribution.

##### Observations and Field Notes

For each site visit, the site-visiting team will conduct direct observations of the clinical work environment and behavior within each *stop* of the patient trajectory. Quantitative observations regarding HAI determinants will be tracked using a structured data form. For example, we will track discrete process of care (eg, antibiotic prophylaxis regimens and preoperative optimization), provider practices (eg, location of driveline exit site), local context and strategies (eg, sink in every patient room and private vs shared patient rooms), and organizational resources (eg, nursing staffing levels). Qualitative observations will focus on examining (1) *context*—circumstances informing data collection (eg, recent line infection mortality); (2) *content*—factual data, locations visited, key process stakeholders, and ward layouts; and (3) *concepts*—hunches or theories about the environment that may help explain a center’s HAI rate (eg, deviations from written protocols) [60].

##### Documents

During each site visit, we will collect relevant protocol documents and interview participants at the relevant transition point about the use of the documents, variations, or other volunteered information. Other relevant documents, patient education documents, postsurgical order sets, and variations by surgeons will be collected.

#### Analytical Approach

##### Qualitative Analysis

Preliminary analysis will begin with a research team debrief at the end of each day, which will reflect team members’ field notes, impressions, and observations. These recorded conversations will provide an additional source of data for defining facility- and unit-level contextual characteristics. Debriefing sessions during day 1 will also identify areas of focus and inquiry for day 2. On day 2, we will explore questions raised on day 1 to develop an expanded understanding. At the end of day 2, the most current version of the toolkit will be presented to the sites for feedback.

##### Developing Case Studies

For each site, we will develop a case study following a structured outline that will have a sufficiently flexible format to accommodate site variation [61]. As the study summary for each site is completed, we will compare the findings with the other sites for the case series analysis. For each site case study, the summary will begin following each visit, when team members will review all qualitative and quantitative sources of data from each site. Team members will then begin the process of coding all the qualitative data including deidentified transcripts using qualitative analysis software (MAXQDA). Team members will convene regularly to compare independent coding of the qualitative data and revise the codebook iteratively until consensus is reached on codes, themes, categories, and coding criteria. This group consensus approach facilitates, enriches, and increases the rigor of data interpretation [62]. The study team will (1) develop findings by meeting regularly to review code summaries and memos created during prior meetings and (2) discuss and interpret the data across low- and high-performing centers. The analysis will occur by site, and findings or new questions will be iteratively explored after completion of each site visit.

#### Integration of Quantitative and Qualitative Analyses

All quantitative (aim 1 findings about the specific sites) and qualitative data (aim 2 findings) will be integrated into the case study for each site. Related findings from both data sources will be matched to provide a comprehensive understanding of each center’s HAI prevention strategies. Multiple case series analyses will be performed. As appropriate for related findings, joint display analysis (ie, the process of iteratively creating, interpreting, and restructuring tables and figures that integrate the quantitative and qualitative findings) will be used to illuminate similarities and differences in HAI prevention strategies across centers and draw overall conclusions [63].

#### Member Checking

Member checking is the process of providing qualitative and mixed methods findings back to study participants to elucidate their input on the overall interpretation [64]. The case study summary for each site will be distributed back to participants who indicated an interest in reviewing the findings. These participants will be asked to indicate their overall agreement with the study findings and to make any corrections or clarifications they deem necessary. Any requisite correction or clarification will be incorporated into the final case study reports used in the case series analysis.

### Aim 3: Develop, Iteratively Enhance, and Disseminate a Best Practices Toolkit for Preventing Health Care–Associated Infections That Accommodates Various Center Contexts

The study team will create a HAI preventive toolkit of evidence-based recommendations that may be customized to the context of each center. The development of the toolkit will be informed by the findings from aims 1 and 2. We will field test our prototype toolkit at the same 10 centers that participated in aim 2. This process will identify approaches for optimizing adoption (ie, fit and suitability for everyday use) as well as inform local context needs and any necessary modifications (eg, content, design, and options). The team will host a dedicated 90-min session at an annual cardiac surgical conference (eg, the International Society for Heart and Lung Transplantation) to elicit further user feedback about the toolkit’s acceptability. We will use the feedback to develop a final toolkit, which will be distributed to US VAD centers. Finally, a follow-up survey will be electronically distributed to US VAD centers to assess national adoption rates of the toolkit.

#### Translation of Findings Into a Draft Toolkit

We will develop an initial version of a printed HAI prevention toolkit of evidence-based recommendations based on the Agency for Healthcare Research and Quality (AHRQ) guidelines [65]. In addition, we anticipate using the RE-AIM framework when considering the components of our toolkit as they relate to the likelihood of reach, efficacy, adoption, implementation, and maintenance [66]. The steps involved in the development of the toolkit are illustrated in Figure 3. The content of the toolkit will be informed by the findings from aim 1 (determinants of center’s HAI rates) and aim 2 (center’s strategies, context, and local resources). The toolkit will be designed to provide local customization to optimize adoption by individual centers. The toolkit will include a self-assessment questionnaire and corresponding educational resources. The self-assessment questionnaire will be designed to locally tailor evidence-based recommendations. The set of educational resources derived from stakeholder interviews will also address local, context-specific needs. We anticipate that the user-friendly toolkit will provide educational resources (eg, impact, prevention, pathophysiology, and epidemiology), prevention strategies (eg, concise summary of evidence-based recommendations with supporting literature).

**Figure 3 figure3:**
[figure not shown]
Development of the health care–associated infection preventive toolkit. HAI: health care–associated infection; INTERMACS: Interagency Registry for Mechanically Assisted Circulatory Support; VAD: ventricular assist device.

#### Field Testing of the Toolkit

The prototype toolkit will be field tested at the same 10 centers that participated in aim 2. Study team members will conduct audio-recorded interviews of VAD clinical stakeholders to elicit user feedback regarding the toolkit’s usability, acceptability, and likelihood of significant effectiveness for preventing HAIs using a *think out loud* approach [67]. Although primarily intended to identify approaches for optimizing adoption (ie, fit and suitability for everyday use), the interviews will inform local context needs and any necessary toolkit modifications (eg, content, design, and options). Study team members will analyze field notes and deidentified transcripts. Iterative versions of the toolkit will be developed and presented at subsequent centers, thus enhancing local stakeholder acceptability and usability. After iterative development across the 10 centers, a fully revised and enhanced version will be sent back to the centers for final review and feedback. A further refined version will be prepared for feedback and presentation at an annual cardiac surgical conference (eg, the International Society for Heart and Lung Transplantation).

#### Broad Ventricular Assist Device Stakeholder Input on the Toolkit

A moderated expert panel will be convened at an annual cardiac surgical conference (eg, the International Society for Heart and Lung Transplantation) to gather stakeholder input on the refined toolkit. During this session, we will share the rationale and intended use of the toolkit and highlight the toolkit’s usability, acceptability, and likelihood of significant effectiveness. Attendees will use an audience response system to provide Likert-scaled responses to each question and will be invited to offer additional qualitative feedback concerning the reasons underlying their quantitative survey responses. Panelists (representing cardiac surgery, heart failure cardiology, infectious disease, and epidemiology) will be invited to respond to attendees’ remarks. The entire session will be double audiotaped (with deidentified transcripts created thereafter). Analysis of the audience response system data and the themes emerging from the discussion for each item will be integrated to draw overall conclusions and inform final revisions of the toolkit. Thereafter, we will distribute the final version to US VAD centers.

#### Assessment of Toolkit Adoption

A follow-up survey intended to assess toolkit adoption rates among US VAD centers will be developed and electronically distributed using the same approach as the center survey described in aim 1. The survey will be pretested to assess face and content validity, comprehensibility, time to completion, and ambiguity. The survey is anticipated to solicit information using a mixture of multiple-choice responses (eg, awareness of the toolkit, roles of those involved with local adoption, identified surgeon champion, types of resource support provided to the adoption team, and frequency of team meetings) and open-ended responses (eg, method used to implement the toolkit, perceived barriers and facilitators for implementation, ongoing quality improvement initiatives to enhance local adoption, and perceived effectiveness of the toolkit).

## Results

The project was funded by the AHRQ in 2018 and enrollment for the overall project is ongoing. We are conducting a systematic review of interventional HAI prevention studies and developing the survey concerning HAI determinants across US VAD centers. We anticipate that survey data collection will begin in November 2019. Findings from aims 1 and 2 will be used to develop a toolkit of evidence-based HAI prevention practices that may be adopted to the local contexts and across VAD centers. The first results are expected to be submitted for publication in 2019.

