**Methods:**

This is a sequential mixed methods study starting with a cross-sectional assessment of current practices. To address aim 1, we will conduct (1) a systematic review of HAI prevention studies and (2) in-depth quantitative analyses using administrative claims, in-depth clinical data, and organizational surveys of VAD centers. For aim 2, we will apply a mixed methods patient tracer assessment framework to conduct semistructured interviews, field observations, and document analysis informed by findings from aim 1 at 5 high-performing (ie, low HAIs) and 5 low-performing (ie, high HAI) centers, which will be examined using a mixed methods case series analysis. For aim 3, we will build upon the findings from the previous aims to develop and field test an HAI preventive toolkit, acquire stakeholder input at an annual cardiac surgical conference, disseminate the final version to VAD centers nationwide, and conduct follow-up surveys to assess the toolkit’s adoption.

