### Aim 1: Identify Determinants of Center-Level Variability in Health Care–Associated Infection Rates

To address this aim, we will first conduct a systematic review of interventional HAI prevention studies. Second, we will supplement the clinical dataset with (1) data from an electronically distributed survey of VAD centers to identify HAI prevention strategies not already tracked through INTERMACS and (2) center-specific measures of provider social network configurations using a merged INTERMACS-Medicare dataset [7,36]. Third, we will calculate center-specific 90-day HAI rates. Fourth, we will model variability in and identify determinants of centers’ HAI rates using this enhanced clinical dataset. We hypothesize that (after accounting for perioperative risk factors through INTERMACS) process, provider, device, and center- and unit-specific risk factors will be significant determinants of HAI rates. Findings will inform the sampling plan and focus on aim 2 activities.

#### Datasets Used for Aim 1

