#### Sample Size

We project analyzing data among 9339 VAD patients receiving durable VAD from 2008 to 2017. We will administer surveys to potential respondents (VAD coordinator, surgeon, and cardiologist) from an estimated 153 VAD centers.

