#### Analytic Approach

First, we will conduct a systematic review of the published literature to identify established HAI preventive practices [44,45]. Second, we will use survey responses to identify provider and institutional practices that contribute to center variability in HAI rates. Third, we will use our linked Medicare-INTERMACS datasets to identify preoperative, intraoperative, and postoperative factors that contribute to center variability in HAI rates.

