##### Primary Endpoint

Our primary endpoint is any HAI 90 days after device implant. We will account for HAI competing risks (eg, death and device removal) and other censoring (follow-up less than 90 days) using time-to-event analysis. Furthermore, we will use 2 approaches for modeling HAI risk. First, we will use the Cox proportional hazards model. We will adjust for surgery year and season and investigate interactions by key biological variables (eg, patient age, sex, and race). We will account for patient demographics (eg, age and sex), disease characteristics (eg, pulmonary disease), and surgical history (eg, prior cardiac surgery) and study the effect of intraoperative care (eg, cardiopulmonary bypass duration) and postoperative care (eg, duration of intubation). We will use the Lasso variable selection method to assess variables for model inclusion [46]. We will handle the multilevel structure (eg, patients are nested within centers) using the robust sandwich variance–based inference or frailty model approach. On the basis of the final fitted model, effects of risk factors will be quantified by hazards ratios and tested by score tests. Second, we will use random survival forest, an extension of the random forest method to right-censored time-to-event data, to model the effects of risk factors nonparametrically [47-49]. The final model will be an ensemble average of fitted trees from bootstrap samples.

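### Practices surveyed as current from November 2019 are used to explain infections after 2008-2017 implants, and no stated step aligns practice with implant date

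*Protocol article*

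**What the plan says.** Outcome period (Protocol article, Sample Size): "We project analyzing data among 9339 VAD patients receiving durable VAD from 2008 to 2017". The survey goes to respondents "from an estimated 153 VAD centers". The Primary Endpoint section states: "Our primary endpoint is any HAI 90 days after device implant". Outcome follow-up therefore closes by about the end of March 2018.

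Timing of the practice measurement: the Abstract (Methods) says "This is a sequential mixed methods study starting with a cross-sectional assessment of current practices", and the Results section says "We anticipate that survey data collection will begin in November 2019".

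Use of the survey: under Analytic Approach for aim 1, "we will use survey responses to identify provider and institutional practices that contribute to center variability in HAI rates". The opening section of aim 1 adds survey data to the clinical dataset and then says "we will model variability in and identify determinants of centers’ HAI rates using this enhanced clinical dataset".

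Aim 2 follows aim 1. Its Sampling section picks 5 low-HAI and 5 high-HAI centers using the aim 1 rates. The visits then record practices, layout and staffing as they stand, partly to help account for those rates.

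**The concern.** The practice variable describes a center in late 2019 or after, while the outcomes belong to patients implanted in 2008-2017. A center that took up a practice in 2016 would be coded as having it for its 2009 patients. A center that dropped a practice before the survey would be coded as never having had it. If the timing of change is unrelated to a center's infection rate, both errors pull the estimated effect toward no effect. If centers took up practices because their rates were high, the association could be distorted or even reversed.

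At stake are the survey part of aim 1 and, through it, the toolkit that aim 3 builds on aims 1 and 2. The Limitations section allows that determinants may not be found and answers by expecting ample variation in practice. A null result caused by mistimed exposure could then be read as absence of a determinant.

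**Working it through.** The article gives no effect size, power or adoption date, so there is no stated figure to reproduce. The check has two parts: what the text fixes, and how large the effect could be under stated assumptions.

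**1. The gap (from the article's dates).**
- Last possible implant, end of 2017, to November 2019: 2019.83 − 2018.00 = 1.83 years.
- First possible implant, start of 2008, to November 2019: 2019.83 − 2008.00 = 11.83 years.

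**2. Whether any stated step closes the gap.**
- Primary Endpoint: adjustment for surgery year and season handles trend in the outcome. It does not change a practice coded as present before it was adopted.
- Exploratory Analyses: the sensitivity analyses concern low-volume centers and missing covariates.
- Teamwork and Communication: the simulations concern errors in the provider networks.
- Limitations: the time gap is not mentioned.

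**3. Truly exposed share among centers that report a practice.** Assumptions, not in the article: implants even over 2008-2017; adoption dates uniform from year L to November 2019; no practice dropped. The pre-adoption share is 0 for adoption before 2008, rises linearly to 1 at the start of 2018, and is 1 after that. Its mean is (5 + 1.83)/(2019.83 − L).

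| Adoption uniform from | Pre-adoption share | Exposed share |
|---|---|---|
| 2008 | 6.83/11.83 = 58% | 42% |
| 2003 | 6.83/16.83 = 41% | 59% |
| 1998 | 6.83/21.83 = 31% | 69% |

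If yearly volume tripled linearly over the decade, the pre-adoption shares become 51%, 36% and 28%.

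For a single adoption date with even volume, adoption at the start of 2010, 2013, 2015 or 2017 leaves 20%, 50%, 70% or 90% of that center's patients before the practice.

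**4. Diluted hazard ratio.** Approximation: apparent HR = exp(exposed share × ln true HR). For a true HR of 0.70, ln 0.70 = −0.357.
- From 2008: exp(0.42 × −0.357) = 0.86.
- From 2003: exp(0.59 × −0.357) = 0.81.
- From 1998: exp(0.69 × −0.357) = 0.78.

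A linear mix, (pre-adoption share × 1) + (exposed share × 0.70), gives 0.87, 0.82 and 0.79, so the choice of approximation matters little.

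**5. Restriction to 2015-2017 implants.** With adoption uniform from 2008, the exposed share is (7 + 1.5)/11.83 = 72%, and a true HR of 0.70 appears as exp(0.72 × −0.357) = 0.77. The cost is sample size: 9339/153 = 61 patients per center, and 61 × 3/10 = about 18 if volume is flat.

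**6. What dilution could cost in power (illustration only).** Assume half the centers adopt, HAI is 60% against 50% when truly exposed, two-sided alpha is 0.05 and the intracluster correlation is 0.05. The design effect is 1 + (61 − 1) × 0.05 = 4. Power is 99.8% with correct dating, 95.5% with a quarter of adopters' patients misdated, 68.6% with half and 23.2% with three quarters. At half misdated, it runs from 90.9% to 45.5% for an intracluster correlation of 0.02 to 0.10.

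**The case against.** The strongest reply is that this is a condensed article. The questionnaire is not shown and was still being written, and it may well ask when each practice began. That limits the point but does not remove it. The dates, the description of the practices as current and their explanatory use are all stated, and nothing in the text qualifies them.

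Several stronger readings are tempting and are not supported:
- A reader might infer that most adopters' patients predate the practice. With even volume that holds only for practices adopted after about the start of 2013. With adoption dates reaching back to 2003 or 1998, the average share is below half.
- A reader might infer that the whole primary-endpoint model is compromised. INTERMACS patient, operative and device data and the claims-based networks are contemporaneous with the implants. Only practices measured by survey or site visit are affected.
- A reader might add device change as a separate unhandled flaw. INTERMACS records device type and the Cox model adjusts for surgery year, so that is at least partly covered.
- A reader might take reversal as expected. The article does not say that centers adopted practices in response to high rates, so reversal is only a possibility.
- A reader might assume that the 10 sites will be labeled by a decade-long average. The Sampling section says only that aim 1 rates will be used and that selection will be refined. Aim 2 is also a qualitative case series in which a practice's history can be asked about, so the hazard-ratio arithmetic does not carry over to it.

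**Conclusion.** The mismatch is real and follows from the article's own dates. As written, the plan would treat practices reported from November 2019 as if they applied to every patient implanted in 2008-2017. Practices that changed during or after that window would be misclassified for some or all of a center's patients, and their effects generally diluted. Practices in place throughout are not affected.

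The size cannot be fixed from the article. Under the three assumed adoption windows, a true HR of 0.70 would appear as somewhere between about 0.78 and 0.86. This rests on even implant volume, uniform adoption dates, no dropped practices and adoption timing unrelated to prior infection rates. The point should be fixed before the survey is fielded. It does not invalidate aim 1 as a whole.

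**What to change.** Before fielding, while the survey is still in development and pretesting:
- For each practice, ask the year adopted and, where it applies, the year stopped. Code the practice as present or absent at each patient's implant date.
- Add a sensitivity analysis limited to the most recent implants in the dataset, for example 2015-2017, especially where dates are unknown.
- State the time gap in the limitations.

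For aim 2, choose or check the 10 sites using shrunken center rates from the most recent years of the existing dataset, and ask at each visit when the key practices began. The article does not say that the team will hold registry data after 2017, so the check should not depend on them.

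Cost: a few survey items and a recoded exposure. Recalled dates will contain error, so dilution is reduced, not removed. The restricted analysis keeps only about 18 patients per center if volume is flat, and on the 2008 adoption assumption still leaves about 28% of adopters' patients misdated.
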